### Adherence and Protocol Deviations

This study allows researchers a high level of control over protocol adherence and deviations. Given that intervention materials are mainly delivered weekly via WhatsApp messages, and only researchers have full control over Fitbit wearable functions, the potential for protocol deviation is minimal. Research staff will perform Fitbit data consistency checks via the Fitbit online dashboard system, which includes (1) monitoring battery life and synchronization status and (2) downloading Fitbit data. Reminders to charge and synchronize the device will be sent via WhatsApp if participants have not done so. Participants are welcome to approach staff should any issues arise. Participants are told to feel free to request withdrawal from the study at any stage.

To investigate the effects of adherence and device wear time, a post hoc analysis will compare participants with consistent wear time to those with inconsistent wear time across all groups.

### Analysis Populations

Primary outcome analysis will be conducted according to intention-to-treat principles. Participants with missing outcome data at the 6-month follow-up will be excluded from the analysis.

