### Sample Size

To ensure sufficient statistical power, we intend to recruit 355 East Asian participants with overweight or obesity. An oversampling strategy has been adopted, with 35.1% (87/248) of the full sample consisting of individuals at a higher genetic risk for T2D. The required number of participants (n=87) for subsample analysis was based on the desired medium effect size (*F*=0.3085), derived from a 3-group comparison. The control group’s average wearable device–measured MVPA time was 80 (SD 35) min/d. The intervention group receiving genetic risk information alone (intervention arm 1) demonstrated minimal changes (85 min/d), while the intervention group receiving combined genetic risk information and wearable device functions (intervention arm 2) was expected to show a difference of approximately 23% in MVPA time (105 min/d; [(105 − 85) / 85 × 100%], corresponding to a difference of 23% in MVPA time compared to previous Fitbit interventions) [26].

Our sample size calculation assumed an α level of 5%, a power of 80%, and a correlation of 0.70 among 3 repeated measures. A total of 355 participants are recruited to ensure the inclusion of an analysis sample of 248, while factoring in an expected attrition rate of 20% (71/355) and an anticipated Fitbit data missing rate of 10.1% (36/355), independent of attrition, considering instances of insufficient battery life or device loss.

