### Analysis Methods

#### Primary Outcome

We will perform primary outcome analysis according to intention-to-treat principles using a series of linear mixed effects models with fixed effects for time, group, and group × time interactions for objectively measured MVPA time, with repeated measures for each participant. Models will be adjusted for potential confounders such as age, sex, and BMI. Adjusted marginal means with 95% CIs will also be presented to compare differences between study groups across all assessment time points.

The analysis will use a longitudinal data analysis model to examine patterns of differences across assessment time points, study groups, and group × time interactions. Results for the group × time interaction term will be included. In addition to the 4 assessment time points, the analysis will also be performed with time as a continuous variable across the study period. The effect modification will also be investigated according to the level of T2D genetic risk, which will be further categorized based on the average T2D genetic risk estimate and educational level of the sample (ie, between college and noncollege graduates). This post hoc categorization can enable us to examine the intervention effects within each group of genetic risk. To ensure fair random assignment of participants between the groups, we will examine between-group differences in the primary outcome data, using an ANOVA test or, if parametric assumptions are not met, a Kruskal-Wallis test.

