#### Sensitivity Analysis and Missing Data

We will conduct two sets of sensitivity analyses: (1) without adjustment for confounders and (2) using an iterative Markov chain Monte Carlo multiple imputation procedure to handle missing data at the 12-month postintervention and 6-month follow-up time points. This procedure assumes that data are missing at random within each group. The randomness of missing data will be tested using the *Amelia* package in R. For variables with missing values (eg, sex, age, educational level, BMI, blood pressure, and handgrip strength at baseline), 5 imputations will be generated for each missing value. To account for nonlinear trajectories in PA patterns, we will conduct additional sensitivity analyses using nonlinear mixed effects models with spline terms to capture nonlinear trajectories in outcome variables.

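### The primary analysis is labelled intention-to-treat but excludes everyone without a 6-month follow-up outcome, which makes it a completer analysis that the planned mixed model does not need

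*SAP article*

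**What the plan says.** Under Analysis Populations the SAP article states: "Primary outcome analysis will be conducted according to intention-to-treat principles". The next sentence reads: "Participants with missing outcome data at the 6-month follow-up will be excluded from the analysis". The Primary Outcome part of Analysis Methods repeats the label and names the model: "We will perform primary outcome analysis according to intention-to-treat principles using a series of linear mixed effects models", with time, group and group × time as fixed effects and repeated measures per participant.

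Three other sections bear on the point:

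- **Sample Size:** "A total of 355 participants are recruited to ensure the inclusion of an analysis sample of 248". The allowances are 20% attrition (71/355) and "an anticipated Fitbit data missing rate of 10.1% (36/355), independent of attrition".
- **Sensitivity Analysis and Missing Data:** one of the sensitivity analyses is run "using an iterative Markov chain Monte Carlo multiple imputation procedure to handle missing data at the 12-month postintervention and 6-month follow-up time points".
- **Trial Objectives and Hypothesis:** an effect of the combined intervention is predicted at the 12-month time point as well as at the 6-month follow-up. Statistical Principles promises group comparisons at every time point.

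**The concern.** The two sentences under Analysis Populations cannot both hold. Having a final-visit value is decided after randomisation. Selecting on it means the arms compared need no longer be the arms that were randomised. The rule also deletes earlier visits that were measured, so a comparison at 12 months would leave out participants whose 12-month MVPA is on file.

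The rule serves no purpose in the chosen model. A linear mixed model fitted to all observed visits gives valid estimates under missing at random without requiring the last visit.

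Differential loss is possible here. Participants know their arm once the intervention starts. Only the two intervention arms receive weekly risk messages, and only arm 2 receives step goals and prompts. The outcome depends on continued wearing, charging and synchronising of the device. What is at stake is a main result reported as intention-to-treat that is in fact a comparison of completers.

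**Working it through.** **1. The plan's own figures (Sample Size).**
- Effect size from means 80, 85 and 105 with SD 35: f = √[mean of (μᵢ − 90)²] / 35 = √[(100 + 25 + 225)/3] / 35 = 10.80/35 = 0.3086 (stated 0.3085).
- Subsample size from the noncentral F for the between-group factor, λ = f²·N·m / [1 + (m − 1)ρ], with m = 3, ρ = 0.70, α = 5% and power 80%: N = 85. Rounded up to three equal groups this is 87, with power 0.815 (stated 87).
- Full sample: 87/248 = 35.1%, and 355 − 71 − 36 = 248. Both agree with the plan.

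**2. How many the rule could remove.**
- Adding the two allowances, as the plan does: 71 + 36 = 107, and 107/355 = 30.1%.
- Combining them multiplicatively: 1 − 0.80 × 0.899 = 28.1%.
- The plan does not say at which visit these losses fall. The number of observed 12-month records discarded therefore cannot be derived. It lies between 0 and 107; if half of those excluded had 12-month data it would be about 54, or 15% of 355.

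**3. Possible bias (illustration; the missingness model is assumed, not taken from the documents).**
Assumptions: no true effect; SD 35; correlation 0.7 between all visits; 30% missing the last visit in each arm; all of these have 12-month data; missingness random in control; in arm 2, the odds of missing multiplied by 1.5, 2 or 3 per SD lower 12-month MVPA.

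Let δ be the amount by which the mean 12-month MVPA of arm 2 completers exceeds that of all arm 2. With equal correlations, the same selection shifts baseline and the last visit by 0.7δ each. The biases are then:
- single visit, 12 months: δ
- single visit, last visit: 0.7δ
- change from baseline, 12 months: δ − 0.7δ = 0.3δ
- change from baseline, last visit: 0.7δ − 0.7δ = 0

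| Completer-rule bias, min/d | OR 1.5 | OR 2 | OR 3 |
|---|---|---|---|
| Single visit, 12 months | +4.1 | +6.7 | +9.5 |
| Single visit, last visit | +2.9 | +4.7 | +6.7 |
| Change from baseline, 12 months | +1.3 | +2.0 | +2.8 |
| Change from baseline, last visit | about 0 | about 0 | about 0 |

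The table shows simulated values; the algebra agrees with them to about 0.1. Likelihood analysis of all observed visits gives about 0 throughout. That follows from the set-up, because missingness depends only on a 12-month value that is always observed.

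**4. Direction.** A second illustration assumes a true difference of 10 min/d and missingness tied to the 12-month value in one arm only.
- Log-odds −0.5 per SD: completer differences of 15.0 at 12 months and 13.5 at the last visit.
- Log-odds +0.5 per SD: 4.9 and 6.4.
- Same mechanism in both arms, or missingness unrelated to outcome: about 10, so no bias.

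**5. Precision.** The unadjusted SE of a pairwise difference at one visit is 35·√(2/n).
- 248/3 = 82.7 per arm: 5.4 min/d.
- 355/3 = 118.3 per arm: 4.6 min/d.

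The second figure is a best case, because it needs a value from every randomised participant at that visit.

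**The case against.** The strongest reply concerns size, not the contradiction.

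- **Extent of loss.** A reader might infer that 30% of participants and their 12-month data will be thrown away. The documents do not support that. The 30.1% is a planning allowance with no visit timing, and anyone who left before 12 months has no 12-month record to lose.
- **Size and direction of bias.** A reader might also infer that the main result will be inflated in favour of arm 2 by 4 to 9.5 min/d. Nothing in the documents establishes that missingness is outcome-dependent in arm 2 alone; the charging and synchronising reminders under Adherence and Protocol Deviations are not limited to one arm. Those figures also concern single-visit comparisons. The plan reports the group × time interaction as well, and there most of the bias cancels against the shifted baseline.
- **Scale.** The introduction cites an average wearable effect of 6 min/d, against which these biases look large. The trial's own planning difference is larger: 105 − 85 = 20 min/d against arm 1 and 105 − 80 = 25 min/d against control.
- **Safeguards.** Multiple imputation under missing at random is prespecified, so a divergence from the completer result would show. The Recruitment part of Trial Population commits to reporting exclusions with reasons.

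All of this stands as a limit on size. It does not rescue the rule. Marginal means at each visit are also planned for comparison, and the named covariates (age, sex, BMI) do not include baseline MVPA. The 12-month interaction keeps some bias, which in the illustration comes only from deleting measured data. The imputation is a sensitivity analysis, so the primary result still rests on completers, and reporting exclusions discloses the loss without preventing it.

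**Conclusion.** The point holds. As written, the primary analysis population is a completer set under an intention-to-treat label, and the rule conflicts with what the chosen model can do. This follows from the text and needs no assumption.

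The size is conditional. Up to about 30% of randomised participants could be excluded if the plan's allowances are borne out and fall on the last visit. Bias in the arm contrast is a risk, not an established result. It requires missingness that relates to activity differently by arm, may go either way, and is about 0 otherwise. Under the one-sided scenario it ranges from about 0 to 2.8 min/d for change from baseline and from 2.9 to 9.5 min/d for single-visit differences. Equal correlations and complete 12-month data are assumed there, and the latter is the upper bound for discarded records. The precision loss is at most 5.4 against 4.6 min/d in the unadjusted single-visit SE.

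The sentence should be changed because it defines the primary analysis.

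**What to change.** Replace the exclusion sentence under Analysis Populations with:

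> All randomised participants with at least one MVPA value are analysed in their assigned arm; the mixed model is fitted to all observed visits and nobody is excluded for missing a visit.

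Move the analysis restricted to participants with 6-month follow-up data to the sensitivity analyses, and call it a completer analysis there.

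The cost is one sentence of wording and the relabelling of one analysis. No new data are needed, and the recruited sample of 355 is unaffected. The abstract reports that formal analysis started in April 2025, so the change should be dated. If results by arm have already been seen, both analyses should be reported side by side.

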### Trial Population

#### Screening Data

No screening data are collected. Participants’ eligibility is assessed on site.

#### Recruitment

We will report the following: (1) the number of participants eligible for baseline assessment, (2) the number of participants randomly assigned to each group, (3) the number of participants who completed the 6-month follow-up, and (4) the number of participants included in the main analysis (recording any exclusion with reasons).

#### Withdrawal and Loss to Follow-Up

Participants are free to request withdrawal from the study at any stage without providing a reason. The number of participants who withdraw due to reasons such as serious adverse events, safety concerns, or the development of health conditions or symptoms is reported for each randomly assigned group at all outcome measurement time points.

#### Baseline Characteristics

The following baseline characteristics will be recorded and summarized for the full sample and by trial arm: (1) age; (2) sex; (3) educational level; (4) body weight and height; (5) BMI; (6) nondominant hand; (7) blood pressure (systolic and diastolic); (8) handgrip strength (both left and right hands); (9) estimated 10-year and remaining lifetime genetic risk for developing T2D; and (10) blood-based metabolic risk biomarkers such as total cholesterol, glycated hemoglobin, high-density lipoproteins, low-density lipoproteins, and triglycerides.

For categorical variables, we will present the proportion and total number of participants within each category. For continuous variables, means and SDs will be presented. If data are skewed, medians and IQRs will be presented instead.

### Analysis Methods

#### Primary Outcome

We will perform primary outcome analysis according to intention-to-treat principles using a series of linear mixed effects models with fixed effects for time, group, and group × time interactions for objectively measured MVPA time, with repeated measures for each participant. Models will be adjusted for potential confounders such as age, sex, and BMI. Adjusted marginal means with 95% CIs will also be presented to compare differences between study groups across all assessment time points.

The analysis will use a longitudinal data analysis model to examine patterns of differences across assessment time points, study groups, and group × time interactions. Results for the group × time interaction term will be included. In addition to the 4 assessment time points, the analysis will also be performed with time as a continuous variable across the study period. The effect modification will also be investigated according to the level of T2D genetic risk, which will be further categorized based on the average T2D genetic risk estimate and educational level of the sample (ie, between college and noncollege graduates). This post hoc categorization can enable us to examine the intervention effects within each group of genetic risk. To ensure fair random assignment of participants between the groups, we will examine between-group differences in the primary outcome data, using an ANOVA test or, if parametric assumptions are not met, a Kruskal-Wallis test.

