### Statistical Principles

We will present 95% CIs with adjusted marginal means to compare differences between groups at each measurement time point (baseline, immediately after the intervention, 12 months after the intervention, and 6-month follow-up). Results for the interaction term will also be presented. Pairwise between-group comparisons will be performed with Bonferroni adjustment. An overall level of statistical significance will be set at α=.05 before adjustment.

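### The primary model neither adjusts for baseline MVPA nor fixes a common baseline mean, and the plan does not name the primary contrast; precision is lost (15% or 49% of variance, depending on the contrast), without bias

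*SAP article*

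**What the plan says.** The Primary Outcome paragraph under Analysis Methods specifies "linear mixed effects models with fixed effects for time, group, and group × time interactions for objectively measured MVPA time". On covariates it says "Models will be adjusted for potential confounders such as age, sex, and BMI". MVPA at baseline is the first of the four measurements of the outcome (Outcomes, Primary Outcome).

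Two kinds of result are promised. Statistical Principles gives adjusted marginal means with 95% CIs "to compare differences between groups at each measurement time point (baseline, immediately after the intervention, 12 months after the intervention, and 6-month follow-up", with Bonferroni-adjusted pairwise comparisons. Analysis Methods adds "Results for the group × time interaction term will be included". Neither section says which of the two answers the primary question, or at which visit.

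The same Analysis Methods section also plans a check of the allocation: "To ensure fair random assignment of participants between the groups, we will examine between-group differences in the primary outcome data, using an ANOVA test", with Kruskal-Wallis as the fallback.

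**The concern.** Because the arms are compared at baseline too, the model leaves the baseline means free to differ. In that model the marginal-mean difference at a follow-up visit is a post-treatment difference adjusted only for the named covariates, so a chance imbalance in baseline MVPA passes into it. The interaction contrast at the same visit subtracts the baseline difference in full. Neither uses baseline MVPA as efficiently as conditioning on it would, although it is collected for the trial and is likely to be a strong predictor of later MVPA.

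At stake are the width of the intervals and the power of the pairwise comparisons, above all in the high-genetic-risk subsample of 87 on which the sample size rests. Since the primary contrast is unnamed, the size of the loss is open as well.

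The balance test is a separate weakness. Under correct randomization it is significant 5% of the time by chance. A non-significant result removes no imbalance.

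**Working it through.** **Inputs (Sample Size).** Means are 80, 85 and 105 min/d, SD 35. The calculation "assumed an α level of 5%, a power of 80%, and a correlation of 0.70 among 3 repeated measures". The subsample is 87, or 29 per arm under the 1:1:1 allocation. The analysis sample is 248, or 82.7 per arm. Three pairwise comparisons with Bonferroni give alpha 0.05/3 = 0.0167.

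**The plan's own figures reproduce.**
- The grand mean is 90, so the effect size is f = √[(10² + 5² + 15²)/3]/35 = 10.80/35 = 0.3086 (plan: 0.3085).
- For the between-groups test over 3 measures, λ = N·f²·3/(1 + 2 × 0.70). With N = 87, λ = 10.35 and power is 81.5%. The minimum N is 85, which equal arms raise to 87.
- 355 − 71 − 36 = 248, and 87/248 = 35.1%.

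**Variance of a between-arm difference at one follow-up visit**, in units of 2·SD²/n, with ρ the correlation between baseline and that visit:
- visit-wise marginal mean: 1
- group × time contrast (change from baseline): 2(1 − ρ)
- baseline-adjusted or baseline-constrained: 1 − ρ²

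At ρ = 0.70 these are 1.00, 0.60 and 0.51. A generalized least squares calculation with four equally correlated visits, comparing the unconstrained and the constrained model, gives the same ratio of 0.51.

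**Gain from adjustment at ρ = 0.70.**
- Against the visit-wise difference: variance down 49%, SE down 1 − √0.51 = 29%.
- Against the change contrast: 0.51/0.60 = 0.85, so variance down 15%, SE down 1 − √0.85 = about 8%.

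**Other correlations (variance reduction).**

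| ρ | vs visit-wise (ρ²) | vs change, (1 − ρ)/2 |
|---|---|---|
| 0.5 | 25% | 25% |
| 0.6 | 36% | 20% |
| 0.7 | 49% | 15% |
| 0.8 | 64% | 10% |

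If age, sex and BMI already explained 10% to 20% of MVPA variance (an assumption), the partial correlation (0.70 − R²)/(1 − R²) would be 0.667 to 0.625. The further reduction for the visit-wise difference would then be 44% to 39%.

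**SE and power for 20 min/d (105 vs 85)**, with SE = 35·√(factor × 2/n) and a two-sided noncentral t test at alpha 0.0167:

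| Contrast | SE, 29 per arm | Power | SE, 82.7 per arm | Power |
|---|---|---|---|---|
| Visit-wise | 9.19 | 39% | 5.44 | 89% |
| Change | 7.12 | 63% | 4.22 | 99% |
| Baseline-adjusted | 6.56 | 72% | 3.89 | 99.7% |

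At 248 analysed, the difference detectable with 80% power, (2.394 + 0.842) × SE, is 17.6, 13.6 and 12.6 min/d.

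**The case against.** A reader might infer that the model ignores baseline MVPA and gives up half the available precision. The text does not support that. Baseline is in the outcome vector, and the interaction term that the plan also reports is a contrast of change from baseline when visit is a factor. It already recovers most of the gain. The 49% applies only if the visit-wise marginal means carry the primary inference. Analysis Methods says that these will also be presented, which can be read as additional output. On the other side, the confidence intervals in Statistical Principles are attached to the marginal means, and its pairwise comparisons are between groups. The text does not settle the matter, and that gap is part of the point.

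Four further objections carry weight:
- In the full analysis sample, power for the planned 20 min/d is already 89% on the least favourable reading.
- The 87 was "derived from a 3-group comparison" with repeated measures. It was not sized for a Bonferroni pairwise test at one visit, so the low subsample power has more than one cause.
- The 0.70 is stated for 3 measures while the trial has four time points, and the plan does not say that baseline is among the three.
- The covariate list is open-ended, so adding baseline MVPA is not ruled out.

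The last objection does not remove the point: an open list leaves the primary model unfixed. As to the balance test, no analysis decision depends on it and it costs no precision. That it concerns baseline is an inference, because its sentence does not use the word.

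**Conclusion.** The point holds in a limited form. The plan states neither a baseline constraint nor adjustment for baseline MVPA, and it leaves the primary contrast unnamed. The cost at ρ = 0.70 is 15% of the variance if the group × time contrast is primary and 49% if the visit-wise difference is. These figures assume that 0.70 applies between baseline and each follow-up visit and that the SD is 35 throughout. They take no account of what age, sex and BMI explain.

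It would go too far to conclude that the results will be biased. Randomization protects both contrasts on average; what is lost is precision. The practical gain is mainly in the subsample of 87, where adjustment lifts power for 20 min/d from 39% or 63% to 72%. In the sample of 248 it is small for that difference. The statement that a significance test can ensure fair assignment is wrong whichever contrast is chosen.

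**What to change.** 1. Name the arm contrast at one stated follow-up visit as primary, and say that the other visits and the interaction are supportive.
2. Estimate it from a constrained longitudinal model: one common baseline mean for all arms and arm-by-visit effects after baseline only, plus age, sex and baseline BMI. Alternatively, use baseline MVPA as a covariate with only the follow-up visits as outcomes.
3. Drop the ANOVA/Kruskal-Wallis balance test and the between-arm comparisons at baseline. Describe baseline MVPA by arm instead.

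The cost is a few sentences in the plan and a small change to the model code. No new data are needed. The choice of contrast should be fixed before any result by arm is seen.

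### Effect modification by genetic risk is promised, but the plan commits to no estimate, interval or test of the difference in effect between risk categories

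*SAP article*

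**What the plan says.** Under Analysis Methods, Primary Outcome, the SAP article describes a series of "linear mixed effects models with fixed effects for time, group, and group × time interactions for objectively measured MVPA time", adjusted for confounders such as age, sex and BMI. On interactions it promises one result: "Results for the group × time interaction term will be included".

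The same section then announces a further question: "The effect modification will also be investigated according to the level of T2D genetic risk". The sentence goes on to say that the categories will rest on the average genetic risk estimate and on "educational level of the sample (ie, between college and noncollege graduates"). The purpose of categorising is given next: "This post hoc categorization can enable us to examine the intervention effects within each group of genetic risk".

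Two other places bear on this. Sample Size describes oversampling, "with 35.1% (87/248) of the full sample consisting of individuals at a higher genetic risk for T2D", and sizes those 87 for a 3-group comparison inside that subsample. Statistical Principles says "Pairwise between-group comparisons will be performed with Bonferroni adjustment" and promises adjusted marginal means with 95% CIs. The interaction term it mentions without naming is, on its natural reading, group × time. No section gives a term that includes genetic risk or education together with group, or a contrast between categories.

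**The concern.** Effect modification means that the difference between arms changes with the modifier. Its null hypothesis is that the arm difference is the same in each category. An analysis within a category has another null, that the arm difference there is zero. The approach described answers the second question, while the question announced is the first.

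The gap matters because two categories of different size, or two small ones, can easily give one significant and one non-significant result when the true effects are identical. With no committed estimate of the difference, nothing in the planned output would guard a reader against taking that pattern as a finding. Higher-risk participants were deliberately oversampled, so readers are likely to ask whether the intervention works differently in them.

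**Working it through.** **Inputs from the SAP article.** Sample Size: means 80, 85 and 105 min/d, SD 35, α 5%, power 80%, correlation 0.70 among 3 measures, 248 analysed, 87 at higher risk. Randomization: equal allocation to three arms. Statistical Principles: Bonferroni for pairwise comparisons, taken here as 0.05/3.

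**Assumptions.** The remaining stratum is 248 − 87 = 161. Arms are equal within strata (29 and about 53.7 per arm), SD 35 holds in both, and the true effect is the same in both. An even split of 124/124 (about 41.3 per arm) is the alternative, because the plan categorises by the average risk and does not say how many fall on each side.

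**Step 1: reproduce the plan's figure.** The grand mean is 90, so f = √[(10² + 5² + 15²)/3]/35 = 10.80/35 = 0.3086 (stated 0.3085). For the between-group F test on 3 measures, λ = f²·N·3/(1 + 2 × 0.70). At N = 87, λ = 0.3085² × 87 × 3/2.4 = 10.35 and power is 0.815. The smallest multiple of 3 that reaches 80% is 87. Also 355 − 71 − 36 = 248 and 87/248 = 35.1%. The plan's figures reproduce, and they show that 87 is sized for a test within the stratum.

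**Step 2: 3-group test in each stratum, equal effects.** Power is 0.815 at 87 and 0.979 at 161. The chance that exactly one is significant is p₁(1 − p₂) + p₂(1 − p₁) = 0.815 × 0.021 + 0.979 × 0.185 ≈ 0.198.

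**Step 3: pairwise contrasts on the mean of three measures.** The SD is 35 × √(2.4/3) = 31.3, and the standard error (SE) in a stratum is 31.3 × √(2/n per arm), so 8.22 and 6.04 min/d for the 87/161 split.

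| Contrast | α | Power at 87 | Power at 161 | Exactly one significant |
|---|---|---|---|---|
| Arm 2 v control, 25 min/d | 0.05 | 0.860 | 0.985 | 15% |
| Arm 2 v control, 25 min/d | 0.05/3 | 0.741 | 0.959 | 28% |
| Arm 2 v arm 1, 20 min/d | 0.05 | 0.682 | 0.911 | 35% |
| Arm 2 v arm 1, 20 min/d | 0.05/3 | 0.515 | 0.820 | 49% |

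**Step 4: a single visit with baseline adjustment.** The SD becomes 35 × √(1 − 0.70²) = 25.0. At 0.05/3, the 87/161 split gives powers 0.743 and 0.960 at 20 min/d (28%) and 0.921 and 0.997 at 25 min/d (8%). The even split gives power 0.893 (2 × 0.893 × 0.107 = 19%) and 0.984 (2 × 0.984 × 0.016 = 3%).

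**Step 5: a direct test.** Simulating equal effects 400,000 times per setting, a z-test on the difference between the two stratum effects rejected in 4.96% to 5.04% of trials.

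**Step 6: precision of the direct test.** On the mean of three measures the SE of the difference is √(8.22² + 6.04²) = 10.2 min/d. Power is 80% at 2.80 × 10.2 ≈ 29 min/d, and about 50% at 20 min/d. For a single visit without baseline adjustment the SE is 35 × √(2/29 + 2/54) = 11.4 min/d (10.9 for the even split), so 80% power needs about 31 to 32 min/d.

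**The case against.** The strongest reply is that the plan is silent, not wrong. The listed terms describe the primary model; effect modification is introduced as something additional, and nothing rules out a three-way term. The sentence on categorisation says what it allows, not how a conclusion will be drawn. This stands in part. A reader might infer that the trial will declare effect modification when one category is significant and the other is not. The plan nowhere says so, and the percentages above apply only if results are read that way.

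Other limits also stand:

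- Asking whether the intervention works in higher-risk people is a legitimate question, and a within-category estimate answers it. It is still not the question of effect modification.
- The within-category sentence names genetic risk only. The role of education in the preceding sentence is ambiguous, so rates for four risk-by-education cells would rest on one reading of it.
- The objectives and hypotheses concern arm comparisons and do not mention different effects by risk or education, and the plan itself calls the categorisation post hoc. This is not a main reading of the trial.
- The 87/161 split is the oversampling target and is not established for a cut at the average risk.
- With intervals in both categories, a reader could derive the difference, since the categories contain different people. The plan does not commit to doing so.

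Article brevity does not dispose of the point: the article lists its model terms, names the interaction it will report and describes how the categories will be used.

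**Conclusion.** The point holds in a limited form. The plan announces an investigation of effect modification, describes only within-category effects, and commits to no estimate, interval or test of how those effects differ.

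The size of the risk depends on assumptions. At the plan's effects and an 87/161 split, disagreement between categories under equal true effects occurs in about 20% of trials for the 3-group test and 15% to 49% for pairwise contrasts on the mean of three measures. With baseline adjustment and Bonferroni it is 3% to 28% across the two splits. At its most favourable (even split, 25 min/d) it is therefore no higher than the 5% of a direct test. A smaller common effect raises it again: at 12.5 min/d, which is an assumption and not a figure in the plan, the baseline-adjusted rate with Bonferroni is about 50%. A general claim that equal effects would often look different is therefore too strong. The mismatch between question and method does not depend on these rates. It affects a subsidiary analysis, not the primary comparison of arms.

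**What to change.** In Analysis Methods, Primary Outcome, state that effect modification is assessed by adding modifier, modifier × time, modifier × group and modifier × group × time to the mixed model, with separate models for genetic risk and for education. Report the between-category difference in arm effect at 12 months and at the 6-month follow-up, each with a 95% CI and an interaction p-value. Keep the within-category effects with CIs as description, and label the whole analysis exploratory.

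The cost is a few sentences and model terms, with no new data. The downside is imprecision: 80% power is reached only for differences of about 29 to 32 min/d without baseline adjustment, more than the 25 min/d planned between arm 2 and control. The result will often be inconclusive, and the text should say that a non-significant interaction does not show equal effects.
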